SAMPLE SIZE Up to 192 participants (up to 96 in Stage 1 and up to 96 in Stage 2).

POPULATION HIV-infected males and females ≥16 years of age presenting with their first episode of CM.

REGIMEN

Table 1: Stage 1 Regimens

| Cohort | N | Induction Step (Step1)  Daily Dose | Induction Following Ampho B Intolerance Step  (Step 2) | Consolidation Step (Step 3)  Daily Fluconazole Dose | Maintenance Step (Step 4) Daily  Fluconazole Dose |
| --- | --- | --- | --- | --- | --- |
| 1A1 | 24 | Fluconazole  1200 mg | N/A | 400 mg  Or 600 mg with RIF | 200 mg |
| 1B1 | 8 | Ampho B-based regimen;  0.7-1.0 mg/kg ampho B | Fluconazole  400-800 mg daily | 400 mg  Or 600 mg with RIF | 200 mg |
| 2A | 24 | Fluconazole  1600 mg | N/A | 400 mg  Or 600 mg with RIF | 200 mg |
| 2B | 8 | Ampho B-based regimen;  0.7-1.0 mg/kg ampho B | Fluconazole  800 mg daily or maximum locally approved dose | 400 mg  Or 600 mg with RIF | 200 mg |
| 3A | 24 | Fluconazole  2000 mg | N/A | 400 mg  Or 600 mg with RIF | 200 mg |
| 3B | 8 | Ampho B-based regimen;  0.7-1.0 mg/kg ampho B | Fluconazole  800 mg daily or maximum locally approved dose | 400 mg  Or 600 mg with RIF | 200 mg |

1 Enrollment to **Stage 1 ended on x/x/2013**.

Fluconazole dose adjustments based on weight must be implemented at the first dose; after entry, fluconazole dose adjustments in response to toxicities should be implemented on a case-by-case basis (see section 7.4).

Table 2: Stage 2 Regimens

| Cohort | N | Induction Step (Step1)  Daily Dose | Induction Following Ampho B Intolerance Step (Step 2)  Daily Dose | Consolidation Step (Step 3)  Daily Fluconazole Dose | Maintenance Step (Step 4) Daily  Fluconazole Dose |
| --- | --- | --- | --- | --- | --- |
| 4 | 24 | Ampho B-based regimen;  0.7-1.0 mg/kg ampho B | Fluconazole 800 mg daily or maximum locally approved dose | 400 mg  Or 600 mg with RIF | 200 mg |
| 5 | 24 | Fluconazole **1600 mg** | N/A | 400 mg  Or 600 mg with RIF | 200 mg |
| 6 | 24 | Fluconazole **2000 mg** | N/A | 400 mg  Or 600 mg with RIF | 200 mg |
| 7 | 24 | Fluconazole **2000 mg plus Flucytosine xx mg** | N/A | 400 mg  Or 600 mg with RIF | 200 mg |

Fluconazole dose adjustments based on weight must be implemented at the first dose; after entry, fluconazole dose adjustments in response to toxicities should be implemented on a case-by-case basis (see section 7.4). **Note that these dose adjustments are recommended only for study-provided fluconazole.**

A5225 Stages 1 and 2 Overview

Flow Chart

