9.2.3 Exploratory Outcomes (to be described in separate analysis plans)

9.2.3.1 Pharmacology (see section 10.0).

9.2.3.2. Antifungal drug susceptibility of cryptococcal isolates.

9.2.3.3 Ability of LFCrAg assay to detect cryptococcal antigen in stored urine, serum, plasma, and CSF.

### 9.3 Sample Size and Criteria for Stages 1 and 2

9.3.1 Stage 1

The team feels that standard dose (400 mg/day) fluconazole would have about 5% DLT as defined in this study. To avoid the toxicity and difficulty of administration of ampho B, the team feels that ≤25% DLT would be acceptable. In the international setting and in participants with HIV and AIDS, the team also has concluded that there likely will be up to a 15% very early mortality rate in any cohort due to CM and/or HIV, not to the dose of fluconazole. Including participants who received very little fluconazole in safety evaluations to determine dose escalation could bias the evaluation either to be too high (if early deaths without toxicity are considered to be DLTs) or too low (if early deaths without toxicity are included in the denominator of the DLT rate). Thus, for primary safety evaluations, very early deaths (prior to Day 4) will not be included in the decision rule whether they experienced a DLT prior to early death or not [French, 2002; Okongo, 1998; Hakim, 2000; van der Horst, 1997; Brouwer, 2004; Pappas, 2004; Bicanic, Meintjes, et al, 2008; and Milefchik, 2008]. Should more than 6 very early deaths be seen in a cohort, enrollment to the cohort will by paused while the team evaluates the events carefully in conjunction with the SMC to consider if there should be study modifications. Secondary evaluations prior to escalation will include all subjects in a failure-time analysis of DLT with early deaths censored if DLT did not occur prior to death.

The dose escalation rule to be used in Stage 1 is:

- 0-3 DLTs; escalate to the next higher dose.
- 4-9 DLTs; do not escalate. This is the MTD.
- > 9 DLTs; the prior dose is the MTD.

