The decision about which doses will be chosen for testing in Stage 2 will be based on: Stage 1 toxicity including the rates of DLT and also the grades and types of toxicity, dose modifications, the duration of treatment interruptions, and the rate of permanent treatment and study discontinuations, and general consideration of efficacy including early CM mortality, CNS clearance (both the rate of clearance and the proportion who clear), and early information on the duration of remission. An additional 24 participants will be randomized to each dose of fluconazole carried into Stage 2. The Stage 2 sample size for ampho B-based regimens will depend on how many fluconazole doses were tested in Stage 1 with the intent of having a total of 48 participants treated with ampho B between the two Stages. The randomization ratio will depend on how many fluconazole doses are tested and on the target ampho B sample size in this stage.

The target sample size of a total of 48 participants on a dose of fluconazole between Stages 1 and 2, and 48 on an ampho B-based regimen is based on:

- Ensuring that the width of a 90% confidence interval (CI) for culture negativity (early discontinuation or death = fail) within a dose or within ampho B-based regimens no wider than 25%.
- Detecting a difference in EFA of about 0.10 log10 CFU/ml CSF/day (about 67% of the s.d.) between two fluconazole doses or between a dose of fluconazole and ampho B with 90% power and a 2-sided 0.05-level test.
- Detecting a 25% difference (e.g. 50% vs. 75%) in efficacy between two fluconazole doses or between a dose of fluconazole and ampho B with 90% power (one-sided alpha=.10 test).
- Having the added ability to detect unusual or unexpected events that occur at a low rate, especially in consideration of those who might not be evaluable for toxicity given very early death. For example, if an unexpected and unacceptable event occurs at a rate of 5%, there is only a 64% chance of seeing one or more rare events in 20 participants evaluable for safety and an 87% chance of seeing one or more rare events in 40 participants evaluable for safety combined over both Stages.

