### 9.5 Analysis

9.5.1 Stage 1

Dose escalation is based on DLT and the decision rules as outlined above. As noted above, between-dose comparisons to select the fluconazole dose(s) to carry forward will largely be descriptive and not formally powered as all information will be factored into this decision.

9.5.2 Stage 2

In this pilot, we intend to combine the data over both Stages for the ampho B-based cohorts and for fluconazole doses that are tested in Stage 2. As noted above, only the confidence interval around the observed DLT rate in each dose will be adjusted for the dose escalation scheme. Analyses will employ appropriate methods such as Fisher’s exact test to compare dichotomous outcomes (e.g., Grades 3 and 4 events; CSF clearance before week 10) between doses or drugs, and t-tests or Wilcoxon tests to compare continuous covariates between two groups (or ANOVA or Kruskall-Wallis tests if three groups including ampho B). In the event all three fluconazole doses are evaluated in Stage 2, tests for trend such as ANCOVA, Cochran-Armitage and Jonckheere-Terpstra tests will be performed. Survival and other measures of time-to-event from study entry will be summarized with Kaplan-Meier estimates and, where appropriate, tested with log rank tests and possibly proportional hazards regression. The duration of the initial hospitalization will need to consider the duration of hospitalization preceding study entry. The focused neurological exam will be analyzed both on an item-by-item basis and also as a summary measure using methods such as mixed models analysis of variance or GEE that accommodate missing data and changing covariates.

The content and schedule of reports to be available to the core team, the SMC, and the full team will be detailed in the Study Monitoring Plan that will be developed prior to the opening of accrual to the study.

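### The two 90% power statements in section 9.3.2 hold only if all 48 per group have evaluable cultures and if an uncorrected test is used; the protocol's own assumptions give about 84–87% for EFA and about 86% for the binary comparison

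*Protocol*

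**What the plan says.** Section 9.3.2 sets the size of each group: "The target sample size of a total of 48 participants on a dose of fluconazole between Stages 1 and 2", with the same number on ampho B. Two of the reasons it lists are power statements.

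- EFA: "Detecting a difference in EFA of about 0.10 log10 CFU/ml CSF/day (about 67% of the s.d".), "with 90% power and a 2-sided 0.05-level test".
- Binary efficacy: "Detecting a 25% difference (e.g. 50% vs. 75%) in efficacy between two fluconazole doses" or between a dose and ampho B, "with 90% power (one-sided alpha=.10 test").

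Three other places bear on these figures.

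- Section 9.3.1 holds that "there likely will be up to a 15% very early mortality rate in any cohort", defines very early as before Day 4, and derives 20–22 evaluable from 24 enrolled. It uses 20–22 with evaluable quantitative cultures for the Stage 1 EFA power.
- Section 9.5.2 says: "Analyses will employ appropriate methods such as Fisher’s exact test to compare dichotomous outcomes". CSF clearance before week 10 is one of the outcomes it lists there. For continuous measures it names t-tests or Wilcoxon tests.
- The Schema, Table 2, lists cohort 7 ("2000 mg plus Flucytosine xx mg") with 24 participants. Stage 1 tested fluconazole alone.

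**The concern.** The EFA statement gives every enrolled participant a usable week 2 culture. A participant who dies before Day 4 cannot supply one, and the protocol plans for such deaths elsewhere. Section 9.1 replaces participants excluded as HIV-negative, as culture-negative at entry, or for withdrawing before any study medication; early deaths are not on that list. The binary statement rests on a test that rejects more readily than the one offered as the example for the analysis.

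These statements are part of the stated basis for the Stage 2 size, and change in quantitative culture is the primary efficacy measure. A reader who takes 90% at face value would treat a null comparison as somewhat more informative than it is. A reader might also carry the 90% over to cohort 7, an arm added without any update to section 9.3.2.

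**Working it through.** **Inputs.** Group size 48, EFA difference 0.10, proportions 50% and 75%, and the alpha levels come from section 9.3.2. The EFA s.d. of 0.15 and the 20–22 evaluable per 24 come from section 9.3.1. The tests come from section 9.5.2.

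**1. EFA, two-sided 0.05**

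Standardised difference d = 0.10/0.15 = 0.667. Noncentrality = d/√(1/n₁ + 1/n₂). Power is the probability that a noncentral t with n₁ + n₂ − 2 degrees of freedom exceeds the critical value.

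The protocol's figure first: at 48 per group the noncentrality is 0.667/√(2/48) = 3.27 and the critical value is 1.986, so power is 89.8% (90.4% by the normal approximation). The 90% is reproduced.

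Evaluable number over two stages: 2 × 20 = 40 to 2 × 22 = 44 per group. As a cross-check, 48 × 0.85 = 40.8.

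| Evaluable per group | Noncentrality | Power | Difference detectable with 90% power |
|---|---|---|---|
| 48 | 3.27 | 89.8% | 0.100 |
| 44 | 3.13 | 87.1% | 0.105 |
| 40 | 2.98 | 83.8% | 0.110 |

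**2. Binary, 50% vs 75%, one-sided 0.10, 48 per group**

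Uncorrected normal approximation with pooled null variance:

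- pooled proportion 0.625; null standard error √(2 × 0.625 × 0.375/48) = 0.0988
- alternative standard error √((0.25 + 0.1875)/48) = 0.0955
- (0.25 − 1.2816 × 0.0988)/0.0955 = 1.292, so power is 90.2%

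This reproduces the protocol's figure. Exact enumeration over all pairs of outcomes gives:

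| Test | Power at 48/48 |
|---|---|
| Uncorrected z-test, enumerated | 89.6% |
| Fisher's exact, one-sided | 85.6% |
| Continuity-corrected normal approximation | 85.9% |

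Fisher's test reaches 90% at about 56 per group (89.9% at 55, 90.5% at 56). Its actual size at 48/48 is about 6.3–6.6% for common true rates between 50% and 75%, against the nominal 10%. That conservatism is the source of the lost power.

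**3. Basis used elsewhere in section 9.3**

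Table 9-3 (secondary endpoints, one-sided 0.05), dichotomous rows:

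| Groups, rates | Stated | Fisher | Uncorrected |
|---|---|---|---|
| 24-24, 20% vs 40% | 34% | 33.3% | 44.6% |
| 48-48, 20% vs 40% | 61% | 62.0% | 69.3% |
| 24-24, 20% vs 50% | 60% | 60.9% | 71.3% |
| 48-48, 20% vs 50% | 90% | 90.8% | 93.5% |

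The table follows an exact or continuity-corrected calculation; the section 9.3.2 statement does not.

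**4. Cohort 7**

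With no Stage 1 participants to add, it stays at 24. EFA power by the same t-test, before any loss of cultures:

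- 24 vs 48: noncentrality 2.67, power 74.9%
- 24 vs 24: noncentrality 2.31, power 61.8%

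**The case against.** **The 90% figures are not wrong.** This stands. Both reproduce and both lead to 48 per group. A reader might infer an arithmetic error, or that the named test fails for EFA; neither is so, since the t-test gives 89.8% at 48.

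**Fisher's exact test is only an example.** This also stands. Section 9.5.2 does not bind the analysis to it, and an uncorrected z-test has 89.6% exact power, so 90% is honest for that test. What remains is that the only two-group dichotomous test the protocol names does not give the stated figure. Table 9-3 covers different endpoints at a different alpha, so it shows two bases in one section, not a contradiction.

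**The evaluability loss is small and may not apply to both endpoints.** The protocol says about 0.10, and 0.105 is close to that; 40 is the pessimistic end of its range. For culture negativity, section 9.3.2 counts death and early discontinuation as failure, so those participants stay in the denominator. A reader might extend the 40–44 to the binary comparison; the documents do not support that.

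**No power is claimed for cohort 7.** Correct. The statements concern fluconazole doses and ampho B, and Table 9-3 already shows lower power for 24-24 and 24-48 groups, though only for secondary endpoints at one-sided 0.05. A reader might conclude that a promised 90% is missed for the combination arm; no such promise exists. The gap is a section not updated for an added arm.

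**Conclusion.** The point holds as a mismatch of assumptions, of moderate weight. On the protocol's own 40–44 evaluable per group, EFA power is about 84–87%, a shortfall of 3–6 points. With Fisher's exact test the binary comparison has about 86%, a shortfall of about 4 points, which disappears if an uncorrected test is specified. The EFA result assumes the stated s.d. of 0.15, normally distributed changes, and the Stage 1 evaluability ratio carried into Stage 2. The binary result assumes 50% vs 75% with 48 in each denominator.

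For cohort 7 the difference is large (EFA power about 75% or 62%, depending on the comparison group), but that is an omission, not a false claim. Nothing here shows that the sample size must grow.

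**What to change.** In section 9.3.2:

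1. Restate EFA power as about 84–87% on 40–44 evaluable per group, or keep 90% and give the detectable difference as 0.105–0.110.
2. For 50% vs 75%, either state about 86% with Fisher's exact test, or keep 90% and name the uncorrected score (z) test in section 9.5.2.
3. Add a sentence that the 48-per-group figures do not cover cohort 7, with its EFA power at n=24: about 75% against a group of 48 and 62% against a group of 24, before loss of cultures.

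The cost is wording and less favourable stated figures. No participants are added and no decision rule changes.

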The precision with which the rate of IRIS can be estimated will depend on the proportion of participants who initiate ART and the time on study between ART initiation and when participants go off study. It should be remembered that this study is relatively short, and it is recommended that ART not be initiated until Step 3 or 4. The time from ART start to development of IRIS (i.e., any IRIS or specifically CNS IRIS) and the proportion with IRIS at pre-specified time points such as 8 or 12 weeks will be estimated by Kaplan Meier methods. The 95% CI on the proportion with IRIS at specified time points will be calculated using Greenwood’s formula.

### 9.4 Monitoring

- - 1. Stage 1 Monitoring

Stage 1 cohorts will be monitored by the core safety team, which will consult with an ACTG-appointed SMC for an unblinded review of each cohort’s safety data prior to escalation to the next cohort. This review will include data from at least 14 days after entry of the last participant on a cohort. The study may be referred to an SMC during Stage 1 as outlined below. The core team will consult with the SMC for an unblinded review of Stage 1 safety and efficacy to choose the fluconazole dose(s) to be evaluated in Stage 2. There will be regular reports of AEs by dose level to the DAIDS clinical representative following the standard reporting schedule for phase I/II studies, and regular reports on accrual and data quality to the entire team.

This study will require rapid assessment of safety and treatment discontinuations, so will use 48-hour form reporting for all AEs and dose modifications and discontinuations. Standard phase I toxicity reports will be distributed frequently to the core safety team that consists of the study chairs, DAIDS clinical representative, statisticians, data manager, and CTS. The core safety team will have periodic calls to review the data, with the frequency depending on the rate of enrollment into the study and the number and type of events reported. Any member of the core safety team may call for an expedited call. The core safety team will decide whether an event is to be considered a DLT. If the core safety team does not unanimously agree, then the event will provisionally be included in the count of DLTs for determining induction regimen escalation. If the number of provisional events prior to full accrual of a cohort impacts the decision about the safety of a particular fluconazole induction dose level, the decision on dose safety will be referred to the SMC for a final decision and enrollment will be suspended until the SMC decision is received. The core safety team might consult with the SMC at other times during a cohort’s enrollment and follow up and may suspend enrollment pending the outcome of such a review. Additionally, should more than 6 very early deaths be seen in a cohort (or a concerning proportion seen early in cohort accrual), or should we see 2 or 3 DLTs in 20-22 participants at a dose level, and 2 of 2 or 2-3 of 3 are associated with hepatic toxicity, the team will evaluate the events carefully in conjunction with the SMC to consider whether there should be study modifications. The SMC and core team will review safety data and the SMC will review preliminary efficacy data prior to opening a new Stage I cohort for accrual.

9.4.2 Stage 2 Monitoring

Safety in Stage 2 of this study will be monitored by the core safety team as above. Data on fluconazole doses will be pooled for core safety team monitoring. Data on ampho B safety will be presented separately. There will be regular reports of AEs (pooled over fluconazole doses) to the DAIDS clinical representative following the standard reporting schedule for phase I/II studies and regular reports on accrual and data quality to the entire team. This study will be reviewed by the SMC at least annually after entry of the first participant on Stage 2.

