The CCTG trial demonstrated improved clinical outcomes with increasing doses of fluconazole [Milefchik, 2008]. The composite 10-week overall response rates (success defined as alive and CSF culture negative) for fluconazole with and without flucytosine are shown in Figure 1. Of note, fluconazole alone for 10 weeks at the highest doses (1600 mg and 2000 mg/day) had clinical success rates over 60%, comparable to the overall success seen when ampho B is used for 2 weeks followed by fluconazole at 400 mg daily. As the CCTG trial was small and principally designed to assess the safety of higher dose fluconazole with and without flucytosine, a larger phase II trial is needed to confirm these findings in multiple settings and to assess the potential of an all oral treatment regimen to supplant the standard ampho B-based regimen.

Higher doses of fluconazole have been safely employed in the treatment of CM [Haubrich 1994], histoplasmosis [McKinsey 1996], candidemia [Rex 2003], and coccidioidomycosis [Galgiani 1993]. When higher dose fluconazole (up to 2000 mg daily) has been used alone, few serious toxic side effects have been observed (granulocytopenia 4%, and increased liver enzyme test 2%; see Table 2-1).

Table 2-1: Summary of Toxicity Events, CCTG Trial

| Toxicity | Fluconazole alone  N (%) | Fluconazole plus Flucytosine  N (%) |
| --- | --- | --- |
| Sweating | 6 (12%) | 6 (15%) |
| Tachycardia | 7 (14%) | 7 (18%) |
| Abdominal pain | 8 (16%) | 5 (12%) |
| Constipation | 8 (16%) | 6 (15%) |
| Diarrhea | 10 (20%) | 7 (18%) |
| Nausea | 29 (59%) | 23 (57%) |
| Vomiting | 27 (55%) | 24 (60%) |
| Weight loss | 9 (18%) | 8 (20%) |
| Anemia | 7 (14%) | 1 (3%) |
| Granulocytopenia (< 500) | 2 (4%) | 7 (18%) |
| Thrombocytopenia (<50K) | 0 | 3 (7%) |
| Hepatic enzyme increase (1.5x) | 1 (2%) | 3 (7%) |
| Alopecia | 6 (12%) | 4 (10%) |
| Dry skin | 9 (18%) | 13 (32%) |
| Increased skin pigmentation | 1 (2%) | 1 (3%) |
| Decreased hearing | 3 (6%) | 5 (12%) |

When higher dose fluconazole has been combined with flucytosine, the expected hematological side effects (granulocytopenia 18% and thrombocytopenia 7%) were easily detected by regular monitoring. In the CCTG trial, doses of fluconazole at 800, 1200, 1600, and 2000 mg with and without flucytosine were evaluated. Four dosing cohorts were employed, with participants randomly allocated between treatment cells. The baseline demographics of that study population are presented in Table 2-2.

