6.3.9 Clinical Assessments

At the visits indicated in the SoE, clinical assessments should be conducted and should be driven by any previously identified or new signs or symptoms or diagnoses that the subject has experienced since the previous visit.

Vital Signs

Vital signs (temperature, pulse, respiratory rate, and blood pressure) must be recorded on the CRFs.

Signs and Symptoms

At entry, all signs and symptoms occurring within 3 days prior to entry must be recorded and keyed within 48 hours. In Stage 1, Steps 1 and 2, beginning on Day 1, all Grade ≥ 3 signs, symptoms, and toxicities, and those that lead to a change in treatment, regardless of grade, must be recorded and keyed within 48 hours. For Stage 1, Steps 3 and 4, and in all of Stage 2, regardless of step, all Grade ≥ 3 signs, symptoms, and toxicities, and those that lead to a change in treatment, regardless of grade, must be recorded.

In addition, in Stages 1 and 2, the identification of symptoms that lead to the evaluations described under section 6.2.3 must be brought to the attention of the study core team via e-mail within 2 weeks after the site’s becoming aware of these symptoms.

Sites must refer to the DAIDS Table for Grading the Severity of Adult and Pediatric Adverse Events, Version 1.0, dated December 2004, which can be found on the DAIDS RSC Web site: [http://rsc.tech-res.com/safetyandpharmacovigilance/.](http://rsc.tech-res.com/safetyandpharmacovigilance/.  ) .

Diagnoses

All diagnoses identified by the ACTG criteria for clinical events and other diseases must be recorded and keyed within 48 hours.

Classification of Progression of Symptoms

In addition, using data generated from evaluations conducted as described under 6.2.3, investigators will classify progression of symptoms as one of the following:

1) microbiological failure (i.e., positive CSF culture)

2) complication of CM (e.g., obstructive hydrocephalus or vascular complications such as venous or arterial thrombosis)

3) IRIS to CM causing increased inflammation after exposure to ART

4) a new CNS OI (e.g., toxoplasmosis, PML, CNS lymphoma)

5) possibly related to CM but mechanism indeterminate

6) other defined complication unrelated to CM.

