## 9.0 STATISTICAL CONSIDERATIONS

### 9.1 General Design Issues

Stage 1 of A5225/HiFLAC is a phase I/II dose escalation study of the safety and tolerability of an inuction-consolidation strategy of high-dose fluconazole alone for the treatment of CM in HIV-infected participants. Dose escalation will occur between fluconazole cohorts but not within them. Escalation and determination of the MTD will be based on the rate of DLT, as defined in the Glossary of Study-Specific Terms. When safety has been evaluated in Stage 1, additional participants will be enrolled in Stage 2 to one or more doses at or below the MTD to provide additional information on safety and to identify the optimum (best safety and efficacy profile) dose of fluconazole. If more than one dose is to be evaluated, participants will be randomized between fluconazole dose levels in Stage 2. Decisions about escalation between fluconazole cohorts in Stage 1 will be made after the last enrollee in a cohort has been observed for at least 14 days or until it has been confirmed whether or not that participant has experienced DLT. The decision about which doses to study in Stage 2 will be made after all participants in cohort(s) with acceptable DLT have been followed for at least 10 weeks. The decision rules for Stage 1 and the definition of the MTD are detailed in sections below.

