In parallel with the fluconazole escalation and efficacy portions of the study, participants will be randomized to standard treatment with an ampho B-based regimen. During Stage 1, the randomization will be 3:1 between fluconazole and an ampho B-based regimen, with 24 participants enrolled in each of the fluconazole cohorts tested. An additional participant will be enrolled to replace each participant excluded for: (a) not being infected with HIV-1; (b) not having a CM positive CSF culture at entry; or (c) refusal/withdrawal of consent prior to taking any study medication, if the participant's Stage 1 cohort is still open to enrollment. Thus, assuming all three fluconazole cohorts are tested, 24 participants will be treated with ampho B in Stage 1. In Stage 2, an additional 24 participants will be enrolled in each of the fluconazole candidate doses identified in Stage 1 based on their safety and efficacy profiles. The randomization ratio between fluconazole and ampho B-based regimens in Stage 2 will depend on how many doses will be evaluated, with the aim of achieving a total of 48 participants receiving ampho B between Stages 1 and 2.

Because of the need to pause between doses in Stage 1 and to pause long enough to confirm efficacy prior to initiating Stage 2, it is difficult to estimate the duration of accrual on this study. We anticipate that accrual may be completed approximately 1 year after all eligible sites are able to begin enrolling. However, pauses between doses in Stage 1 must be factored in.

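### Section 9.4.2 was not updated for Cohort 7 (fluconazole 2000 mg plus flucytosine): on its natural reading the untested combination is monitored inside a fluconazole pool that dilutes its toxicity

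*Protocol*

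**What the plan says.** Section 9.1 describes Stage 1 as testing a "strategy of high-dose fluconazole alone for the treatment of CM in HIV-infected participants". Table 2 of the Schema then lists a fourth Stage 2 arm, Cohort 7 with N = 24, as fluconazole "2000 mg plus Flucytosine xx mg". Section 3.0 also introduces this arm. Section 9 never mentions it, and Table 5-2 still shows Cohort 7 as a fluconazole dose to be determined.

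On Stage 2 monitoring, section 9.4.2 states "Data on fluconazole doses will be pooled for core safety team monitoring". AE reports to the DAIDS clinical representative are likewise pooled over doses. The only exception named is "Data on ampho B safety will be presented separately". In Stage 1, by contrast, section 9.4.1 has the DAIDS reports made by dose level. On the committee, section 9.4.2 says "This study will be reviewed by the SMC at least annually after entry of the first participant on Stage 2".

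Section 9.4.2 also refers back to the Stage 1 process for the core safety team. That process (9.4.1) includes frequent toxicity reports, expedited calls, DLT adjudication, consultation of the SMC at other times, a trigger at more than 6 very early deaths in a cohort, and a hepatic trigger based on 2 or 3 DLTs among 20-22 participants at one dose level.

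The Glossary defines a DLT as an interruption of the fluconazole induction dose for at least 3 days because of toxicity related to fluconazole. The only other toxicity category, TLT, concerns ampho B.

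**The concern.** Stage 2 was built to validate doses that had each passed a Stage 1 safety review. Cohort 7 has not passed one. The background evidence for this exact fluconazole dose with flucytosine is 8 volunteers (Table 2-2). Section 2.1.2 names marrow suppression as the main flucytosine toxicity, and Table 2-1 shows more granulocytopenia and thrombocytopenia when flucytosine is added.

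If the core safety team sees only a figure averaged over three arms, a problem confined to Cohort 7 is shrunk towards the two monotherapy arms. Two features add to this. A cytopenia attributed to flucytosine is not a DLT as defined. The imported triggers also need cohort-level counts, which a pooled report does not supply. What is at stake is how quickly an excess of toxicity in the least-tested fluconazole arm would be recognised while participants are still being enrolled.

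**Working it through.** **1. The plan's own detection figures.** Section 9.3.2 gives the chance of seeing at least one event with a true rate of 5% as 64% with 20 evaluable and 87% with 40 over both stages.
- 1 − 0.95^20 = 0.642 and 1 − 0.95^40 = 0.871, so both reproduce.
- Cohort 7 has no Stage 1 data. With 20-22 evaluable it has 0.642 to 0.676 (1 − 0.95^22 = 0.676), not 0.87.

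**2. Dilution of the expected toxicity.** The denominators from Table 2-2 are 9 + 16 + 16 + 8 = 49 on fluconazole alone and 8 + 8 + 16 + 8 = 40 with flucytosine. Table 2-1 gives granulocytopenia in 2 and 7 participants, and thrombocytopenia in 0 and 3. Applied to 48 participants in Cohorts 5 and 6 and 24 in Cohort 7:
- Granulocytopenia: (48 × 2/49 + 24 × 7/40) / 72 = (1.96 + 4.20) / 72 = 8.6%, against 17.5% in Cohort 7.
- Thrombocytopenia: (0 + 24 × 3/40) / 72 = 1.8 / 72 = 2.5%, against 7.5% in Cohort 7.

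**3. Dilution of the DLT rate.** Section 9.3.1 takes up to 25% as acceptable. Assume a true DLT rate of 40% in Cohort 7 and a common rate p in Cohorts 5 and 6, with 24 evaluable per arm. An observed rate above 25% means at least 7 of 24 in Cohort 7 alone, or at least 19 of 72 in the pool. The first is a binomial tail. The second is the tail of the sum of Binomial(48, p) and Binomial(24, 0.40).

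| p in Cohorts 5 and 6 | Pooled true rate | P(observed > 25%), Cohort 7 alone | P(observed > 25%), pooled |
|---|---|---|---|
| 5% | 16.7% | 0.90 | 0.01 |
| 10% | 20.0% | 0.90 | 0.10 |
| 15% | 23.3% | 0.90 | 0.31 |
| 20% | 26.7% | 0.90 | 0.57 |

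At p = 10%, 20 evaluable per arm gives 0.87 alone and 0.12 pooled, and 22 gives 0.93 and 0.14.

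The pooled true rate (2p + p7)/3 reaches 25% only when Cohort 7's rate p7 equals 0.75 − 2p. That is 65%, 55%, 45% or 35% for p of 5%, 10%, 15% or 20%.

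**4. The triggers against the pooling.** The early-death and hepatic triggers are counted in one cohort or at one dose level, so neither can be evaluated from a three-arm total. Dose level alone does not settle it either, because Cohorts 6 and 7 are both at 2000 mg. Merging those two at 10% and 40% gives (0.10 + 0.40)/2 = 25%, which is exactly the limit.

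**5. Reporting speed.** Section 9.4.1 announces 48-hour form reporting for all AEs. Section 6.3.9 requires 48-hour keying of signs, symptoms and toxicities in Stage 1 Steps 1 and 2. For "in all of Stage 2, regardless of step, all Grade ≥ 3 signs, symptoms, and toxicities" it asks only that they be recorded. Section 6.3.13 does the same for laboratory toxicities. Section 6.3.7 (treatment modifications) and the diagnoses paragraph of 6.3.9 keep 48 hours with no stage limit.

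**The case against.** The strongest reply is that the protocol offers more protection than the pooling sentence suggests. The study is open-label. Premature discontinuations of fluconazole or ampho B in Step 1 or 2 reach the core team by e-mail within 3 business days (section 7.0). Hematology is drawn at days 4 and 7 and at every scheduled visit from week 2 to week 10. Section 7.1 acts on any Grade 4 toxicity whatever its attribution, so such an event would appear as a treatment modification. Section 2.1.1 reports that haematological effects of the combination were readily picked up by routine monitoring. Report content is left to a Study Monitoring Plan (9.5.2) that is not at hand. All of this stands as protection of the individual participant. None of it gives the team an arm-specific rate or a usable trigger.

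It is also fair that placing Cohort 7 in the pool is an inference. The Schema and section 3.0 treat fluconazole doses and fluconazole plus flucytosine as distinct alternatives, and pooling is stated for the core team and DAIDS reports, not for the SMC. If Cohort 7 is outside the pool, however, section 9.4.2 says nothing about how it is reported, so the text needs changing either way.

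Four stronger readings are tempting and are not supported:
- **The SMC sees Stage 2 only once a year.** The text sets a minimum, and the Stage 1 process allows consultation at other times. What is true is that no earlier look is guaranteed, and ad hoc referral depends on a team reading pooled tables.
- **Stage 2 has no 48-hour keying.** Modifications and diagnoses keep it. The gap is a conflict between sections over signs, symptoms and laboratory toxicities.
- **Cohort 7 would be full before the first annual review.** The statement "We anticipate that accrual may be completed approximately 1 year after all eligible sites are able to begin enrolling" covers the whole study and is qualified in the same paragraph. Cohort 1 took about 20 months to enrol 29 (section 2.1.1), which would be about 29/20 × 12/4 = 4 per arm per year over four equal arms. The Cohort 2 closing date and both Cohort 3 dates are placeholders. No enrolment figure can be fixed.
- **The 9.3.1 count boundary should be applied to Cohort 7.** Its outcomes are escalation and MTD calls, which do not fit a combination arm with no next dose.

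**Conclusion.** The concern holds in this form: section 9.4.2 was not adapted to an arm that skipped Stage 1, and its pooling rule works against the cohort-level triggers it imports. On the natural reading, the expected granulocytopenia signal is halved (17.5% to about 8.6%). The chance that an unacceptable DLT rate shows above 25% drops from about 0.90 to about 0.10 in the central scenario.

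The granulocytopenia figures rest on carrying over rates from a small background trial (7/40 and 2/49, all doses combined) and on 24 participants per arm. The DLT rates of 40% and 5-20% are assumptions. The pooled probability depends strongly on the rate in the other arms (0.01 to 0.57), but at every value examined it is well below the figure for Cohort 7 alone. The DLT-definition gap and the conflict over 48-hour reporting rest on the text alone. All of these points should be settled before Stage 2 opens, because separate reporting introduced late cannot recover a signal missed during enrolment.

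**What to change.** In section 9.4.2:
- Tabulate Cohort 7 separately from Cohorts 5 and 6 in every core-team, DAIDS and SMC report. Cohorts 5 and 6 may stay pooled.
- For Cohort 7, count toxicity related to either fluconazole or flucytosine in the DLT tabulation, and add this to the Glossary definition.
- State that the cohort-level review triggers of 9.4.1 are applied to Cohort 7 on its own data, kept apart from Cohort 6.
- Schedule one early by-arm SMC look at Cohort 7, tied to a stated number of its participants having been followed through day 14. The team should set that number.

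Reconcile the 48-hour reporting of all AEs in 9.4.1 with sections 6.3.9 and 6.3.13, so that the timing for Stage 2 signs, symptoms and laboratory toxicities is unambiguous, at least for Cohort 7.

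The cost is one additional SMC call, somewhat faster keying for 24 participants and one more column in the safety tables. Because the study is open-label, separate tabulation breaks no treatment blind.
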